# MOntelukast as a potential CHondroprotective treatment following Anterior cruciate ligament reconstruction (MOCHA Trial): study protocol for a double-blind, randomized, placebo-controlled clinical trial

**DOI:** 10.1186/s13063-021-05982-3

**Published:** 2022-01-31

**Keywords:** Anterior cruciate ligament, Montelukast, Posttraumatic osteoarthritis, MRI, Biomarker

## Abstract

**Background:**

After anterior cruciate ligament (ACL) reconstruction, patient-reported outcomes are improved 10 years post-surgery; however, cytokine concentrations remain elevated years after surgery with over 80% of those with combined ACL and meniscus injuries having posttraumatic osteoarthritis (PTOA) within 10–15 years. The purpose of this multicenter, randomized, placebo-controlled trial is to assess whether a 6-month course of oral montelukast after ACL reconstruction reduces systemic markers of inflammation and biochemical and imaging biomarkers of cartilage degradation.

**Methods:**

We will enroll 30 individuals undergoing primary ACL reconstruction to participate in this IRB-approved multicenter clinical trial. This trial will target those at greatest risk of a more rapid PTOA onset (age range 25–50 with concomitant meniscus injury). Patients will be randomly assigned to a group instructed to take 10 mg of montelukast daily for 6 months following ACL reconstruction or placebo. Patients will be assessed prior to surgery and 1, 6, and 12 months following surgery. To determine if montelukast alters systemic inflammation following surgery, we will compare systemic concentrations of prostaglandin E2, monocyte chemoattractant protein-1, and pro-inflammatory cytokines between groups. We will also compare degradative changes on magnetic resonance imaging (MRI) collected 1 and 12 months following surgery between groups with reductions in early biomarkers of cartilage degradation assessed with urinary biomarkers of type II collagen breakdown and bony remodeling.

**Discussion:**

There is a complex interplay between the pro-inflammatory intra-articular environment, underlying bone remodeling, and progressive cartilage degradation. PTOA affects multiple tissues and appears to be more similar to rheumatoid arthritis than osteoarthritis with respect to inflammation. There is currently no treatment to delay or prevent PTOA after ACL injury. Since there is a larger and more persistent inflammatory response after ACL reconstruction than the initial insult of injury, treatment may need to be initiated after surgery, sustained over a period of time, and target multiple mechanisms in order to successfully alter the disease process. This study will assess whether a 6-month postoperative course of oral montelukast affects multiple PTOA mechanisms. Because montelukast administration can be safely sustained for long durations and offers a low-cost treatment option, should it be proven effective in the current trial, these results can be immediately incorporated into clinical practice.

**Trial registration:**

ClinicalTrials.govNCT04572256. Registered on October 1, 2020.

**Supplementary Information:**

The online version contains supplementary material available at 10.1186/s13063-021-05982-3.

## Background

After anterior cruciate ligament (ACL) reconstruction, patient-reported outcomes are improved 10 years post-surgery [1]. Cytokine concentrations, however, remain elevated years after surgery with over 80% of patients with combined ACL and meniscus injuries developing posttraumatic osteoarthritis (PTOA) within 10–15 years after injury [2, 3]. Since pain nociceptors are not located in the articular cartilage, patient-reported outcomes improve despite progressive, irreversible cartilage loss, thus making PTOA a “silent killer” [4]. Because early cartilage loss progresses without pain and dysfunction, the prevalence of PTOA continues to increase. PTOA now represents the most common cause of military disability [5, 6] and is increasingly more common in the general population with more than 5.6 million Americans suffering from PTOA [7, 8].

Our recent results illustrate the downstream cytokine and degradative enzyme activity following ACL reconstruction. ACL and meniscus injury initiate a biochemical cascade resulting in cartilage degradation [9–11], and this process involves an upregulated pro-inflammatory response with a dysregulated anti-inflammatory response [12, 13]. Single-dose intra-articular anti-inflammatory treatment has been reported to reduce hyaline cartilage degradation shortly after the time of injury based on synovial fluid measures of type II collagen degradation [4]. The intra-articular inflammatory milieu at the time of surgery appears to predict the patient symptom state 2 years later [14]; however, the effectiveness of preoperative anti-inflammatory treatments in impacting patient symptoms or slowing long-term PTOA progression is as yet unclear. A lack of efficacy in preoperative interventions may be attributed to a profound inflammatory stimulus from surgical reconstruction of the ACL. The postoperative inflammatory cascade results in articular cartilage and meniscus degradation due to matrix degrading enzymes, especially those which breakdown type II collagen [15].

PTOA affects the whole joint organ including the cartilage, synovium, and bone. PTOA progression is multifaceted and includes activation of the pro-inflammatory NFκB pathway, an increase in pro-inflammatory M1 macrophages, cell senescence, and bone remodeling [16–20]. Limiting the biochemical cascade through an innovative disease-modifying treatment to target upstream activity will potentially treat all components of the knee, thereby lessening the inflammatory response, reducing cartilage catabolism, and potentially improving pathologic bony remodeling observed after ACL reconstruction. The early proteomic PTOA response is more similar to inflammatory rheumatoid arthritis than idiopathic OA [13]; thus, long-acting agents which better regulate pro-inflammatory cytokine activity may more successfully limit tissue destruction [21]. By repurposing approved therapeutics with proven immune efficacy [22], we may arrive at a readily available and cost-effective strategy for disease modification.

Montelukast was first approved for clinical use in 1998 for prophylaxis and chronic treatment of asthma. The drug selectively inhibits the cysteinyl leukotriene CysLT1 receptor. Montelukast blocks the actions of cysteinyl leukotriene LTD4, which is produced through the arachidonic acid pathway. This pro-inflammatory signal is released from several cells including the inflammatory mast cells and eosinophils [23].

Montelukast may also address multiple PTOA mechanisms by inhibiting cysteinyl leukotrienes. Cysteinyl leukotriene inhibition in animal and laboratory models of PTOA resulted in the elimination of senescent cells, reduced NFκB activation, and decreased concentrations of pro-inflammatory and catabolic factors and reactive oxygen species (ROS) while increasing expression of anti-inflammatory factors (inducing anti-inflammatory M2 macrophage infiltration), inhibiting osteoclastogenesis, and improving bone quality [24–29]. The novel use of oral montelukast offers the potential of a disease-modifying treatment to prevent irreversible cartilage loss after ACL injury. The purpose of this multicenter randomized, placebo-controlled trial is to assess whether a 6-month course of oral montelukast after ACL reconstruction reduces systemic markers of inflammation and biochemical and imaging biomarkers of cartilage degradation. Our overarching hypothesis is that a 6-month postoperative course of oral montelukast will reduce PTOA progression after ACL reconstruction by inhibiting multiple targets.

## Methods/design

### Aims

The primary aim of this trial is to determine if a 6-month course of daily oral montelukast alters the biochemical mechanisms of PTOA when compared to placebo. The secondary aim is to assess the effect of oral montelukast on cartilage degradation and bone remodeling after ACL reconstruction. The hypotheses for the primary and secondary aims are that the use of montelukast after ACL reconstruction will:
Reduce peripheral concentrations of prostaglandin E2 (PGE2), monocyte chemoattractant protein-1 (MCP-1), and pro-inflammatory cytokines.Reduce degradative changes on magnetic resonance imaging (MRI) at 1 year, in association with reductions in early biomarkers of cartilage degradation (C-terminal crosslinked telopeptide type II collagen (CTXII)) and bony remodeling (an alpha isomerized version of the C-terminal crosslinked telopeptide of type I collagen (CTXIα)).

The complimentary aims will allow assessment of the joint as an organ and provide evidence for a novel, disease-modifying treatment approach with an approved, readily available, and widely used therapeutic agent to target multiple mechanisms of PTOA.

### Participants

Participants will include 30 individuals undergoing primary ACL reconstruction (15 in the treatment group and 15 in the placebo group). Potential study participants will be identified by members of the research team during regularly scheduled office visits at the University of Kentucky’s Orthopaedic & Sports Medicine or University of California San Francisco Sports Medicine Center. After being identified as a potential study participant, the patient will meet with a member of the research team coordinator. Provided that the patient meets all inclusion and exclusion criteria, a member of the research team will begin the process to obtain informed consent. As part of the consent process, patients will have the option to allow the investigative team to store their data and biological specimens for future ancillary studies. We routinely recruit subjects from these physicians’ practices using similar methods.

In March, 2020, the FDA required a Boxed Warning about serious mental health side effects for montelukast which includes the risks of suicidal behavior and other serious neuropsychological events [30]. Children and adolescents will be excluded from the current trial as neuropsychological side effects of montelukast have been reported to be more common in children and adolescents than adults [31, 32]. To further avoid the potential for exacerbation of a pre-existing psychological condition, we will also exclude those with depressive symptoms and those that endorse suicidal ideation at the time of enrollment. Psychological screening and safety monitoring will be described in more detail below.

This trial will specifically target those that may be at greatest risk of a more rapid PTOA onset (age range 25–50 with concomitant meniscus injury as evidenced on their clinical preoperative MRI and clinical exam) [33–35]. Those who are undergoing revision procedures will be excluded; however, patients will not be excluded if they have had a previous contralateral ACL injury and/or surgery. In doing so, we hope to address the needs of the most at-risk patients but also those in whom a treatment signal could be feasibly detected.

#### Age ≥ 25–50

The response to injury may differ between younger and relatively older patients. In a large cohort study, increased age at the time of surgery was identified as an independent risk factor for radiographic PTOA [33, 34]. Additionally, the initial insult of ACL injury is commonly associated with subchondral bone marrow lesions [36]. While midterm outcomes for younger patients do not appear to be impacted by the presence of bone marrow lesions, older patients have demonstrated self-reported pain, functional limitations, and greater cartilage degradation [19, 37, 38]. Patients > 25 years of age may then display worse symptoms and more rapid PTOA progression thereby potentially providing a signal that may be more readily monitored when compared to younger patients. For these reasons, we have elected to enroll individuals between 25 and 50 years of age.

#### Concomitant meniscus injury

Similar to increased age, the presence of meniscus injury was identified as an independent risk factor for radiographic PTOA in a large cohort study [33, 34]. The role of the meniscus injury on PTOA progression may be related to the persistent intra-articular inflammatory response seen after ACL reconstruction [2, 15]. We have demonstrated that pro-inflammatory stimulation of meniscus cells increases matrix metalloproteinase and cytokine activity [10, 15, 39]; the combination of pro-inflammatory cytokines and compressive loading, comparable to sporting and high demand activities, results in further degradative enzyme activity and increased production of pro-inflammatory mediators [40]. In this way, the meniscus plays an active role in promoting the cycle of articular cartilage degradation and PTOA progression after ACL reconstruction. We therefore opted to specifically target patients with concomitant meniscus injury. We will include patients with either medial or lateral meniscus tears evident on preoperative MRI, but should an enrolled participant be found to not have a meniscus tear at the time of surgery, the participant will not be randomized and will be removed from the study. The size, location, and type of meniscal tear will be documented at the time of surgery as will details related to the surgical treatment (repair vs. meniscectomy).

### Design and setting

This is a multicenter, superiority RCT with parallel group assignment and 1:1 allocation ratio to assess the use of montelukast after ACL reconstruction. The study has been approved by both the University of Kentucky and University of California San Francisco institutional review boards. Details of the study design are set out in Fig. 1 according to the Standard Protocol Items: Recommendations for Interventional Trials (SPIRIT) Statement [41]. The SPIRIT Checklist can be found in Additional file 1. Participants will be enrolled at two academic medical centers (University of Kentucky and University of California San Francisco) with study-related analyses being performed at the Cleveland Clinic and Duke University. Important protocol modifications will be communicated to the investigative team through regular weekly meetings. It will be the PI’s responsibility to update participants or trial registries on any protocol modifications.

**Fig. 1 Fig1:**
[figure not shown]
Schedule of enrollment, interventions, and assessments

### Intervention

Patients aged 25 to 50 years will randomly be assigned to receive one daily oral montelukast (10 mg) versus oral placebo daily for 6 months after surgery. Montelukast tablets will be encapsulated in in blue and white gelatin capsules (F05280-1000, Capsuline, Dania Beach, FL) with corn starch filler used to fill the remaining space (Batch/Lot number 176537, Medisca, Plattsburgh, NY). The oral placebo will be the same cellulose capsule with only starch filler. Both the study drug and placebo will be prepared by each institution’s Investigational Drug Service. An oral placebo was selected to offset the potential perceived advantages of daily oral drug delivery ensuring that any treatment effect would be due to the study drug and not differences in drug appearance, mode of delivery, and/or dosing frequency and duration. Prostaglandins and leukotrienes mediate inflammation and are produced through the metabolism of arachidonic acid; blocking the production of these mediators has been shown to have potential anti-inflammatory and chondroprotective effects [42, 43]. Oral montelukast is a selective leukotriene receptor antagonist and, as previously described, induces anti-inflammatory M2 macrophage infiltration, inhibiting osteoclastogenesis and improving bone quality [24–29].

In addition to the aforementioned anti-inflammatory and chondroprotective effects, montelukast was selected based on 3 other key criteria: (1) oral administration, (2) postoperative timing of use, and (3) sustained method of delivery.

#### Oral administration

In our recent experience with studies involving intra-articular injections with ACL-injured patients (NCT02930122), we have observed that a relatively high percentage of eligible subjects (31%) chose not to participate in the studies specifically because they would be undergoing an intra-articular injection and/or having a “fear of needles.” Oral montelukast may overcome or lessen this barrier as it has been reported to be preferred by asthmatic patients and thereby engenders greater compliance when compared to inhalants [44]. The current study will allow us to assess the feasibility and acceptability of montelukast compared to our previous experiences with intra-articular agents (NCT02930122) [4, 15].

#### Postoperative administration

The ability to initiate montelukast 10 days after surgery offers multiple advantages. First, we have previously described the logistical challenges to enroll patients within 8 days of injury in order to administer intra-articular anti-inflammatory injections [9]. Perhaps more important than early preoperative patient access is the ensuing surgical insult to the joint. While we have demonstrated that preoperative corticosteroid injection reduces biomarkers of cartilage degradation [4], the surgery reinitiates a secondary inflammatory response [15]. Further, this inflammatory response after ACL reconstruction was both larger in magnitude and duration when compared to the initial ACL rupture [15]. Intra-articular concentrations of pro-inflammatory cytokines, interleukin-6 (IL-6), and IL-1β, were nearly twofold greater 1 week post-surgery than 1 week after the initial injury. IL-6 and IL-1β were remained significantly elevated 4 weeks following ACL reconstruction when compared to concentrations assessed on the day of surgery [15]. These results suggest a potential need for postoperative treatments that may be of critical importance to alter the biochemical joint catabolic cascade induced by surgery that likely contributes to progressive cartilage degradation and PTOA. Moreover, it may be necessary to alleviate the overwhelming biochemical surgical insult before it is possible to discern any real benefits of early post-injury interventions.

#### Sustained delivery

We have previously reported that the proteomic changes after ACL injury are more similar to changes associated with rheumatoid arthritis than idiopathic osteoarthritis [13]. This response is not only reinitiated after surgery, but is maintained perhaps indefinitely as increased synovial concentrations of pro-inflammatory cytokines have been reported 5 years after ACL reconstruction [2]. It has been previously suggested that long-acting agents may provide a greater treatment effect as temporal regulation of cytokine activity may more successfully alter the pro-inflammatory environment than shorter-duration treatments [21]. Prior studies have shown that montelukast can counteract the inflammatory environment of rheumatoid arthritis [45]. As such, similar to the treatment of rheumatoid arthritis, a sustained treatment may be necessary to modify the PTOA disease process, providing additional justification to test a 6-month course of oral montelukast after ACL reconstruction.

#### Safety monitoring

A safety review of treatment group will be performed with safety endpoints being monitored at each study visit. Due to an FDA black box warning related to montelukast, we will utilize the Patient Health Questionnaire-9 (PHQ-9) to quantify depressive symptoms and suicidality at all clinic-based study visits. The PHQ-9 is a validated, self-administered screening instrument that asks patients to select how often they have been bothered by specific symptoms in the last 2 weeks [46, 47]. The PHQ-9 consists of 9 questions that parallel the diagnostic criteria for Major Depression Disorder from the Diagnostic and Statistical Manual of Mental Disorders. Each item is scored from 0 to 3 with 3 representing more severe symptoms. PHQ-9 scores range from 0 to 27, and scores of 15 or greater are indicative of severe depression [46]. After providing informed consent, patients will complete a baseline PHQ-9 questionnaire. Should the subject have a PHQ-9 ≥ 15 at baseline, they will be withdrawn from the study. If the patient is not currently being observed and/or treated for depression, they will be then referred to their primary care physician or mental health professional for evaluation. The PHQ-9 also has a question that is specific to suicidal thoughts. Should the subject endorse suicidal ideation at baseline, the subject will be withdrawn from the study prior to initiating treatment and a “warm hand-off” will be performed and a risk assessment will be performed by the local psychologist that is a part of the study team.

##### Study stopping rules

Neuropsychiatric symptom severity and suicidality will be monitored closely within study procedures and reviewed weekly by the study’s medical officer and the principle investigator, and referrals for appropriate levels of care will be done as needed. At all study postoperative follow-up visits, subjects will complete the PHQ-9. Similar to the enrollment screening procedures, treatment will be immediately stopped for subjects with scores ≥ 15 or if they endorse suicidal ideation. The subject will then be referred to their primary care physician, mental health professional, or the study’s local psychologist that is a part of the study team as described above. In addition, consistent with the FDA’s guidance [30], treatment will also be immediately stopped if patients experience a change or increase in any of the following behavior or mood-related changes:

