#### Adherence

Adherence to the treatment protocol will be assessed and verified through the completion of the drug log. The drug log will be maintained by unblinded study personnel and inspected on no less than an annual basis by an unblinded study co-investigator.

Patient adherence to the medication will be documented through weekly patient self-report. The patients will be asked to take 1 pill daily during the 6-month prescription, thus 1 day will equate to 1 pill. Patients will be provided a weekly SMS text notification with a link to REDCap to ask if the patient has taken the medication that day. Previous literature has defined good medication compliance as taking at least 80% of the prescribed medication [55]. We will calculate the proportion of patients who meet this criterion in the treatment group as well as the 95% confidence interval (CI) around this compliance rate. The treatments will be considered feasible and acceptable if over 70% of participants reach this threshold.

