### Data collection

#### MRI analyses

All subjects will undergo MRI examination at visit 4 (1 month after ACL reconstruction) and visit 6 (12 months postoperatively). At one of the enrollment sites, the average time between initial presentation to the orthopedic surgeon and the date of surgery is 9 days. As such, it is often difficult logistically for patients and/or their caregivers to attend a study-specific MRI visit preoperatively when they have already had to take time away from school or work to have the clinical MRI performed in order to confirm the original injury diagnosis. Thus, we will rely on the clinical MRI and clinical exam to determine eligibility and have opted to have the baseline research protocol MRI images collected 1 month postoperatively as this is more feasible for patients and this timing is consistent with other groups studying cartilage changes after ACL reconstruction [56].

At both enrollment sites, sagittal and axial MRI images will be acquired using a 3.0-T MRI scanner and an 1Tx/15Rx phased array knee coil/flex coil. Sagittal and axial T1-weighted fast spin echo images (FSE) will be acquired to allow semiquantitative analysis at the conclusion of the study. These sequences will be followed by a sagittal high-resolution 3D dual echo steady state (DESS) sequence for cartilage segmentation and a sagittal combined T1ρ/T2 mapping for the quantification of cartilage composition. The major parameters for the DESS sequences are as follows: FOV = 140 mm, matrix = 384 × 307 × 176, resolution = 0.36 × 0.45 × 0.7 mm^3^, time of repetition (TR)/time of echo (TE) = 17.6 ms/6.0 ms. The T1ρ/T2 mapping will be acquired using a 3D MAPSS sequence with major parameters: FOV = 140 mm, image matrix = 320 × 160 × 24, resolution = 0.44 × 0.44 × 4 mm^3^, time of recovery = 1.5 s, bandwidth = 400 Hz/Pixel, TR/TE = 7 ms/3 ms, time of spin lock (TSLs) = 0, 10, 40, 80 ms for T1ρ mapping and preparation TEs = 0, 20, 40, 60 ms for T2 mapping. The scan time will be approximately 12 min for the combined T1ρ/T2 mapping. Images will be obtained with the knee in full extension.

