#### Patient-reported outcomes

In addition to the aforementioned assessments of depressive symptoms with the PHQ-9 questionnaire, we will also be assessing knee-related patient-reported outcomes at the five clinic-based study visits using the Knee injury and Osteoarthritis Outcome Score (KOOS). The KOOS is comprised of 5 subscales (Pain, Symptoms, Activities of Daily Living, Sports and Recreation, and Quality of Life) with each scale being scored from 0 to 100 with higher scores being indicative of a superior outcome [60]. In addition, we will calculate the KOOSglobal score, which is a global score indicative of overall knee symptoms and function that has been validated in ACL reconstruction patients [61], as well as the patient acceptable symptom state (PASS) from the KOOS quality of life domain [14, 62].

At the 6- and 12-month follow-up visits, participants will also be asked to complete the single patient acceptable symptom state (PASS) question, which requires the participant to consider all aspects of life to determine if the state of the knee is “satisfactory” 1 year following surgery and postoperative treatment [63]. The specific phrasing of the PASS question will be, “Taking into account all the activity you have during your daily life, your level of pain, and also your activity limitations and participation restrictions, do you consider the current state of your knee satisfactory?” to which the participants will have the option to respond either “yes” or “no” [63].

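### As described, no PHQ-9 is given between months 1 and 6, so for most of the dosing period the stop rule depends on participants volunteering symptoms

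*Protocol article*

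**What the plan says.** The Participants section explains that the drug has carried a boxed warning since March 2020 covering suicidal behavior and other serious neuropsychological events. The response is in Safety monitoring and Study stopping rules:

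- The PHQ-9 is used "to quantify depressive symptoms and suicidality at all clinic-based study visits". Study stopping rules adds: "At all study postoperative follow-up visits, subjects will complete the PHQ-9".
- "Neuropsychiatric symptom severity and suicidality will be monitored closely within study procedures and reviewed weekly" by the medical officer and the principal investigator.
- Treatment stops at once for a score of 15 or more or for endorsed suicidal ideation. Separately, "treatment will also be immediately stopped if patients experience a change or increase in any of the following behavior or mood-related changes", followed by a list of 17 items.

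On timing, the abstract says: "Patients will be assessed prior to surgery and 1, 6, and 12 months following surgery". MRI analyses places imaging at "visit 4 (1 month after ACL reconstruction) and visit 6 (12 months postoperatively"). Patient-reported outcomes refers to "knee-related patient-reported outcomes at the five clinic-based study visits".

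The weekly participant contact is described under Adherence. It is a "weekly SMS text notification with a link to REDCap to ask if the patient has taken the medication that day".

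**The concern.** The plan treats suicidal ideation on study drug as a reason to stop at once, and at visits it asks about it directly. The schedule gives one such form about three weeks into dosing and the next when the course is ending or nearly so. In between, no described step asks a participant about mood or suicidal thoughts. Someone who develops symptoms in months 2 to 5 and does not raise them could stay on drug until the month-6 visit. That form asks about the preceding two weeks, so it may also miss an earlier episode.

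The stake is participant safety. The schedule is the same in both arms, so no bias between arms is in question, and the power calculation is not touched.

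**Working it through.** The document gives no figure for this interval, so there is none to reproduce. The check has two parts.

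**Which visits fall between months 1 and 6?**

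- The abstract lists assessments before surgery and at months 1, 6 and 12.
- MRI analyses numbers month 1 as visit 4 and month 12 as visit 6. Only visit 5 lies between them, so visit 5 is month 6.
- Biomarker analyses takes specimens on the day of surgery and at every postoperative study visit, and Primary aim analysis has four time points. 4 - 1 = 3 postoperative visits, which matches months 1, 6 and 12.
- Of the five clinic-based visits, 5 - 3 = 2 are earlier. One may be a pre-dose visit around day 10. It would precede month 1 and would not shorten the interval.

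The other contacts described do not ask about mood. The calls in Minimizing attrition are attendance reminders, and the study check named for routine-care visits (Study stopping rules) is of the incision.

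**How long is the interval, and what share of dosing is it?**

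Inputs: dosing starts 10 days after surgery (Study stopping rules) and lasts six months (Intervention). The article does not say whether it ends at the 6-month visit or six full months after day 10, so both are shown. The PHQ-9 look-back is two weeks (Safety monitoring). One month = 365.25/12 = 30.44 days.

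- Interval: 5 × 30.44 = 152.2 days; 152.2/7 = 21.7 weeks.
- Dosing from day 10 to month 6: 182.6 - 10 = 172.6 days; share 152.2/172.6 = 88%.
- Dosing for six full months from day 10: 182.6 days; share 152.2/182.6 = 83%.
- Outside any look-back: 152.2 - 14 = 138.2 days = 19.7 weeks; 138.2/172.6 = 80%, or 138.2/182.6 = 76%.

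With visits at day 28 and day 182 instead, the interval is 154 days (22.0 weeks) and the shares are 154/172 = 90% and 154/182 = 85%, so the result does not hinge on the month convention.

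**After the fix.** With four more forms in the interval, the days outside any look-back fall from 138 to 152.2 - 5 × 14 = 82. The longest interval between forms falls from 152 days to about 30 if the forms are timed from surgery. If they are timed from day 10, the month-2 form falls on day 10 + 60.9 = 70.9, so the longest interval is 70.9 - 30.4 = 40 days.

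**The case against.** The strongest objection is that this is a condensed article. Between-visit questions and alert routing often sit in a full protocol or manual; the article itself mentions a manual of procedures, and the schedule figure is not shown. This stands as a caveat: an unnumbered remote check cannot be ruled out. It does not remove the point, because the article states when the PHQ-9 is given and how the visits are numbered, and that stated schedule serves the stated stop rule poorly.

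A reader might infer that the promise of weekly review is contradicted. The text does not support that. The sentence sets how often two people review, and may mean reviewing whatever has come in. With staggered recruitment at two sites, such a review has a purpose. Stopping at once can likewise mean on detection, and the symptom-list rule can act on any report at any time. Nor does the Adherence section say the text message can contain nothing else; it describes one question.

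There are real mitigations. Minors, people with a baseline score of 15 or more and people with baseline suicidal ideation are excluded. A PHQ-9 is given about three weeks into dosing, and participants can reach staff from 7:30 am to 5 pm. These reduce the risk, but none of them asks a participant about mood in months 2 to 5.

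It is also tempting to go further and screen weekly for every listed symptom. Several items, such as trouble sleeping, restlessness and feeling anxious, are plausible after knee surgery in either arm, and the rule stops treatment on any of them. A weekly checklist could trigger many stops unrelated to the drug.

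**Conclusion.** The point holds as a worthwhile safety improvement. Following the plan as described, 152 days (83-88% of dosing) pass between PHQ-9 forms, and about 20 weeks (76-80%) are covered by no PHQ-9. In that time the weekly review and the stop rule rely on participants volunteering symptoms.

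This rests on the visit schedule as reconstructed above, on dosing from day 10, and on there being no remote check in documents not shown. It is not evidence of an internal contradiction, of bias, or of a trial with no safety monitoring. The number of additional stops that more frequent screening would produce cannot be estimated from the document, which gives no symptom rates.

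**What to change.** Send the PHQ-9 through the existing REDCap text link once a month at months 2, 3, 4 and 5 of dosing. Put crisis-contact wording on the form and set an automatic alert to the medical officer. State that these answers feed the weekly review.

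Apply the existing stop rules unchanged. On a score of 15 or more, or any endorsed suicidal ideation, the participant is told to stop the study drug at once. The medical officer's call follows for assessment and referral and is not a condition for stopping. Keep the clinic forms and thresholds as they are, and do not add a weekly checklist of the 17 listed symptoms. Those that the PHQ-9 does not cover would still depend on spontaneous report between visits.

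If the full protocol already has a between-visit check, one sentence naming it is enough.

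Costs: a few REDCap fields, an IRB amendment, alert handling outside 7:30 am-5 pm, and some additional precautionary stops in both arms. The article replaces subjects who leave the study before the 6-month visit and prepares 40 randomization slots for 30 participants. It does not say whether stopping the drug counts as leaving, so the amendment should settle that.
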